**Treatment Assignment and/or Randomization**

If participants meet eligibility criteria and a signed consent form has been received from a parent/guardian, they may be contacted and scheduled for a baseline session. For participants aged 18 years, baseline sessions may be scheduled prior to obtaining consent (as consent will be obtained at baseline prior to administering any study procedures). For all participants, a member of the study team will discuss the consent/assent form with the participant, provide answers to any questions, and, if the participant is interested, a licensed clinician will obtain informed consent/assent. The participant will then be given a signed copy of the consent/assent form.

Once enrolled and after the baseline phase (EMA Phase 1; Baseline as Usual), participants will be scheduled for randomization, which will employ a 2-arm, within-subject, parallel group design to examine effects of short- and longer-term withdrawal across 8 weeks of cannabis abstinence on depression and SI. Participants will be randomized to 8 weeks of abstinence with contingency management (CB-Abst: n=100) or non-contingent monitoring with no abstinence requirement (CB-Mon: n=100) using a 1:1 ratio in blocks of 6. A subset of study staff who will administer surveys and questionnaires querying about mood and suicidality will be blind to group assignment. Randomization will be based on a computerized scheme developed by the study statistician. Randomization will be stratified by age (<=14 years old vs >=15 years old), sex (male vs female), and depression severity (mild/moderate vs. Moderately severe/severe). A key aspect of the approach is that the 8-week period is long enough to observe true changes due to cannabis discontinuation, separate from effects of cannabis withdrawal and residual cannabinoid exposure. Groups will complete 1-week of EMA in weeks 1 (EMA Phase 2; Randomized Withdrawal) and 8 (EMA Phase 3; Randomized Sustained Abstinence) of the randomized study period.

Individuals randomized to monitoring who incidentally stop using cannabis, or express an interest in discontinuing cannabis, will not be removed from the study. If desired, these individuals will be provided with substance use resources at the time of interest in cessation.

1. **STUDY PROCEDURES**

Study procedures are nearly identical to those used in IRB approved pilot protocol (#2021P002416).

**Screening (V0):** School-wide screening will take place on site and at the participating schools (as part of #2021P001873), and/or over the phone. Data will be collected during the screening to determine eligibility for the study.

*Measures to be completed by participants:*

- School-wide screening instrument (as part of #2021P001873; only for participants recruited through schools)
- Telephone screener
- Universal screener (as part of #2024P002895)

**Baseline Visit (V1):** Participants will attend an approximately 3-hour baseline visit to be conducted on the campus of the participating school, at a local library, at Massachusetts General Hospital, or virtually via video conferencing (via MGB-approved video conference platforms like Microsoft Teams or zoom). The baseline visit will initiate a 2 week-long baseline phase involving smartphone EMA during which they will use cannabis per usual to quantify the temporal relationship between use and mood and SI, and the within- (e.g., concurrent other substance use, social contexts) and between-subject factors (e.g., severity of cannabis use, depression, and SI) that moderate these linkages. We will ensure that this 2-week baseline phase does not coincide with when there are anticipated major deviations from typical patterns of cannabis use (e.g., family vacation, exam week).

*Eligibility confirmation to be completed prior to obtaining consent:*

Patient Health Questionnaire-9 (PHQ-9)

*Measures to be completed by participants following consent:*

- Timeline Followback Interview (TLFB)
- Substance Use History
- Marijuana Craving Questionnaire – Short form (MCQ-SF)
- Cannabis Withdrawal Scale (CWS)
- Marijuana Motives Measure (MMM)
- Drug Testing
- Ecological Momentary Assessment (EMA) Training
- The Reasons of Living for Adolescents (RFL-A)
- Self-injurious Thoughts and Behaviors Interview-Revised (SITBI-R)
- Child Behavior Checklist Youth Self Report (CBCL)
- Columbia Suicide Severity Rating Scale (C-SSRS)
- Pittsburgh Sleep Quality Index (PSQI)
- Mini International Neuropsychiatric Interview (MINI) Kid 7.0.2: Cannabis Use Disorder and Major Depressive Episode
- Beck Anxiety Inventory (BAI)
- Alcohol Use Disorder Identification Test (AUDIT)
- The Cannabis Use Disorder Identification Test (CUDIT)
- Penn State Electronic Cigarette Dependence (ECDI)
- Connors ADHD Self-Report Index (ASRI)
- Psychiatric History
- Concomitant Medications
- Demographics
- *Fitbit Set-up

* For virtual participants, Fitbits will be sent immediately following the baseline visit and set-up asynchronously

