**Inclusion Criteria**

1. Ages 12-18;
2. Current daily or near daily cannabis use (i.e., use ≥ 4 days per week on average; Timeline Followback);
3. Score ≥ 5 on PHQ-9;
4. Access to an internet-capable smartphone (iOS or Android);
5. Provision of at least 1 collateral contact for risk monitoring;
6. Provision of informed assent (or consent if 18 years) and parent/guardian consent if <age 18;
7. Approximately 50% response rate to EMA prompts during the first EMA phase (Baseline as Usual);
8. No immediate plan to discontinue cannabis use in the next 3 months;
9. Positive toxicology result for cannabis on baseline urinalysis.

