At the end of 2 weeks, the app will automatically discontinue EMA surveys. Two 1-week EMA phases will occur during the randomized period (weeks 1 and 8 post randomization; Figure 1). Staff will re-train participants on the EMA app prior to each of these EMA phases. Staff members will monitor EMA compliance and will reach out proactively to participants failing to meet criteria. After the third and final EMA phase, participants will be reminded that they will no longer need the EMA app, and that they can delete it (see figure 1 study schema for illustration of EMA administration periods).

All EMA surveys, regardless of phase of the study, will consist of short, multiple-choice items with logic-branched follow-up items. Within each of these surveys, participants will be queried on social settings and activities, cannabis and other substance use, mood, and suicidal ideation. See sections below detailing our plan for data monitoring to ensure safety in the event of SI exacerbation.

**Actigraphy Component (Fitbit): P**articipants will participate in a study component that collects sleep and activity data via a Fitbit Inspire 3. Participants will wear the watch after enrollment at Visit 1 through the Visit 12 (approximately 70 days after enrollment). To enhance compliance, participants will be paid a $25 compliance bonus at each of the three EMA phases data is available for 16/24 hours of 80% of days within that phase.

| **Passive Parental Consent** | **Parental/student consent/assent** |  | **Cannabis users in CM discontinue cannabis use** |  |  |  |  |  |  |  |  |  |  |  |  |
| --- | --- | --- | --- | --- | --- | --- | --- | --- | --- | --- | --- | --- | --- | --- | --- |
|  | **V0** |  | **BL (V1)** | **V2** | **V3** | **V4** | **V5** | **V6** | **V7** | **V8** | **V9** | **V10** | **V11** | **V12** | **Exit interview** |
| Days since Baseline |  |  | 0 | 14 | 16 | 19 | 21 | 28 | 35 | 42 | 49 | 56 | 63 | 70 |  |
| Fitbit Inspire 3 |  |  | x | x | x | x | x | x | x | x | x | x | x | x |  |
| Phone Screener | x |  |  |  |  |  |  |  |  |  |  |  |  |  |  |
| EMA Assessments  (x indicates when EMA assessment phases begin) |  |  | x | x |  |  |  |  |  |  |  |  | x |  |  |
| *Substance Use Questionnaires* |  |  |  |  |  |  |  |  |  |  |  |  |  |  |  |
| AUDIT |  |  | x |  |  |  |  |  |  |  |  |  |  |  |  |
| CUDIT |  |  | x |  |  |  |  |  |  |  |  |  |  |  |  |
| CWS |  |  | x | x | x | x | x | x | x | x | x | x | x | x |  |

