Payments will be made using an escalating scale for abstinence reimbursements and on a consistent scale for EMA compliance (see Tables 1 & 2). The reimbursement schedule was informed by PI’s ongoing contingency management studies and has been effective in other populations (Worden et al., 2017). Maximum total earnings will be matched across group to not confound the potential effects of monetary payments and depressive symptoms and SI. Attendance payments paid via Advarra will be issued at the end of every in-person visit (when participants provide urine samples), abstinence payments will be made between visits when abstinence is biochemically confirmed, and EMA payments will be issued at the end of each of the three EMA phases.

| **Table 2: Max Overall Study Remuneration Schedule** | |
| --- | --- |
| **EMA Compliance Phase 1 (approximately 80%) completion** | $100 |
| **Or: EMA Compliance Phase 1 (approximately 50%) completion** | $25 |
| **Fitbit Compliance Phase 1 (66%) completion** | $25 |
| **EMA Compliance Phase 2 (approximately 80%) completion** | $100 |
| **Or: EMA Compliance Phase 2 (approximately 50%) completion** | $25 |
| **Fitbit Compliance Phase 2 (66%) completion** | $25 |
| **EMA Compliance Phase 3 (approximately 80%) completion** | $100 |
| **Or: EMA Compliance Phase 3 (approximately 50%) completion** | $25 |
| **Fitbit Compliance Phase 3 (66%) completion** | $25 |
| **Study Visits/ Abstinence** | $445 |
| **Overall Fitbit and EMA Bonus (completion across whole study)** | $50 |
| **Max Total Earnings $870** | |

Participants will earn either $100 for a compliance rate of approximately 80% or $25 for a compliance rate of approximately 50% across each of the three EMA phases and $25 for a Fitbit compliance rate of 66% across each of the three phases. Participants can earn an additional $50 if they achieve an overall compliance rate for both Fitbits and EMA phases across the entire study. Payments will be made at the study completion. If a Fitbit device is lost or not returned, 20% of the total earned for this portion of the study will be deducted.

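### A fixed block size of 6 printed in the protocol, with a loosely worded EMA response criterion judged just before randomization, lets unblinded staff know about 23% of assignments in advance

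*Protocol*

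**What the plan says.** All references are to the Protocol.

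- **Allocation** (Treatment Assignment and/or Randomization). The control arm and the block structure are given as "non-contingent monitoring with no abstinence requirement (CB-Mon: n=100) using a 1:1 ratio in blocks of 6". The source of the list is one sentence: "Randomization will be based on a computerized scheme developed by the study statistician".
- **Strata** (same section). "Randomization will be stratified by age (<=14 years old vs >=15 years old), sex (male vs female), and depression severity" (two levels), so 2 × 2 × 2 = 8 strata.
- **Blinding** (same section). "A subset of study staff who will administer surveys and questionnaires querying about mood and suicidality will be blind to group assignment". Assessment Techniques repeats this for mood and suicidal ideation measures. No other staff are said to be blind.
- **Visibility of the arm** (Remuneration). "abstinence payments will be made between visits when abstinence is biochemically confirmed", and abstinence is paid only in CB-Abst. Staff who handle these payments know the arm.
- **Entry check** (Inclusion Criteria, item 7). "Approximately 50% response rate to EMA prompts during the first EMA phase (Baseline as Usual"). No lower limit, denominator or decision-maker is named.
- **Timing** (Treatment Assignment and/or Randomization; visit schedule). "Once enrolled and after the baseline phase (EMA Phase 1; Baseline as Usual), participants will be scheduled for randomization". V2 falls on day 14.
- **Contact with low responders** (Assessment Techniques). "Staff members will monitor EMA compliance and will reach out proactively to participants failing to meet criteria".

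**The concern.** With one known block size, anyone who has seen the earlier allocations in a stratum knows the rest of the block as soon as three places in one arm are filled. That matters only if someone can act on the knowledge. Here a participant becomes eligible, or not, on a threshold with no exact value, at about the moment the next assignment falls due. A borderline responder could be accepted, chased for more prompts or turned away with the likely arm in mind, even without intent.

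If that happened, the arms would differ at entry in compliance or motivation, and no later analysis could reliably remove the difference. The comparison most exposed is the first Helmert contrast under Protocol non-adherence (CB-Mon against all CB-Abst), which the protocol calls the intent-to-treat comparison.

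**Working it through.** The protocol gives no predictability figure, so there is none to reproduce.

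**Inputs from the protocol:** ratio 1:1; block size 6; 8 strata; target 200. **Assumptions:** the observer knows the block size, has seen every earlier allocation in the stratum in order, and knows the new participant's stratum.

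**1. One complete block.** A block of 6 with three places per arm has 6!/(3!3!) = 20 equally likely orders. An assignment is certain when only one arm has places left.

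- Places 1 to 3: never certain.
- Place 4: certain if the first three are alike, 2 × (3/6 × 2/5 × 1/4) = 0.10.
- Place 5: certain if the last two are alike, 2 × 4/20 = 0.40.
- Place 6: always certain, 1.00.

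The sum is 0.10 + 0.40 + 1.00 = 1.5 per block, or 1.5/6 = 25%. The general formula for block size 2m, 2m/(m + 1), gives 6/4 = 1.5 at m = 3.

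**2. Average guessing.** Always naming the arm with more places left is right with probability 0.5, 0.6, 0.6, 0.7, 0.7 and 1.0 at places 1 to 6. The sum is 4.1, and 4.1/6 = 68.3%, against 50% by chance.

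**3. 200 participants in 8 strata.** The mean per stratum is 200/8 = 25, and the last block is usually incomplete. If its filled length is equally likely to be 0 to 5, it holds 2.5 participants on average. The expected certain assignments in it are 0, 0, 0, 0, 0.1 and 0.5 for those lengths, a mean of 0.1. Per stratum this gives (25 − 2.5) × 0.25 + 0.1 = 5.725, so 5.725/25 = 22.9%, and 8 × 5.725 = 45.8, about 46 participants.

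Simulation agrees: 22.8% to 23.0%, with correct guessing about 67.4%. Skewed strata (assumed 10%/90% by age and 60%/40% by severity) give the same result.

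**4. Varying block sizes.** Simulated with 200 participants in 8 strata, sizes equally likely, and an observer who knows the set of sizes but not their order:

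| Block sizes | Certain in advance | Correct guesses |
|---|---|---|
| 6 only | about 23% | about 67% |
| 4 and 6 | about 5.5% to 5.8% | about 68.5% |
| 4, 6 and 8 | about 2.2% to 2.4% | about 67% |

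Varying the sizes removes most certain predictions but not the general guessing advantage.

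**5. Width of the entry criterion.** At 7 to 9 prompts a day for 14 days, Phase 1 delivers 98 to 126 prompts; the power table uses 112. Half of 112 is 56. If, as an illustration only, anything from 45% to 55% were treated as borderline, that would run from about 50 to 62 completed prompts. How many participants would fall in such a band cannot be derived from the protocol.

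**The case against.** Several points on the other side are fair.

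- **Fixed blocks within strata are conventional.** True. Varying the sizes is better practice, not the correction of an error.
- **Tracking is laborious.** An observer must log allocations in order in 8 strata of about 25 participants, or four blocks each, with visits spread over schools, libraries, the hospital and video. The protocol also does not say whether the V1 or V2 PHQ-9 sets the severity stratum. If it is V2, the stratum is known only at the randomization visit. So 23% is the most that a fully informed observer could know, not an expected rate of misuse.
- **Who judges item 7 is not stated.** It may be someone unaware of allocations. The response rate is logged by the platform and is not a clinical judgement.
- **Borderline cases may be few.** The exploratory study reports 76% of prompts completed on average. That figure is attached to participants who completed all phases, so it does not settle how many fall near 50% in Phase 1.
- **The main Aim 2 analysis is already selective.** It keeps only CB-Abst data with confirmed abstinence, a selection made after randomization, and Aim 1 is not randomized. A reader might infer that predictable blocks undermine the trial's main comparison. The protocol does not support that; what is exposed is mainly the intent-to-treat contrast.
- **Concealment details may sit elsewhere.** One-at-a-time release of assignments is operational and may be in a document not shown, so its absence is not counted here.

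What stands is narrower: the block size and the inexact criterion are both fixed in this protocol, and no separate randomization document can make a published block size unknown.

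**Conclusion.** The point holds as a low-severity, cheap improvement. For unblinded staff who track a stratum, about 23% of assignments (roughly 46 of 200; 25% in complete blocks) are certain in advance, and an entry criterion without an exact limit is settled just before the next assignment.

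The size rests on full knowledge of past allocations and of the stratum. Two stronger readings are tempting and should not be drawn. One is that entry is being steered: the protocol shows an opportunity, not an occurrence. The other is that upcoming assignments are generally predictable: about three in four are not certain, and best guessing is right about 67% of the time.

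**What to change.** 1. **Treatment Assignment and/or Randomization.** Delete the block size. State that permuted blocks of randomly varying size are used within strata, with sizes and order held only by the study statistician. Sizes 4, 6 and 8 serve here only to show the effect (certain assignments at about 2.5% or less even if the set is known); the sizes actually used should not appear in the protocol.

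2. **Inclusion Criteria, item 7.** Replace the approximate wording with an exact cut-off, for example at least 50% of delivered Phase 1 prompts, computed from the EMA platform and recorded before the assignment is requested. This step is needed because varying blocks alone leave the average guess rate near 67%.

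**Cost.** The unused part of the list is regenerated and one sentence is amended in each of two places. Sample size, visits and participant burden do not change. Chance imbalance within a stratum can be slightly greater: at most 4 with a block of 8, against 3 with a block of 6. Simulated overall imbalance between arms is unchanged, with a median of 2 and a 95th percentile of 6 under both schemes. A few borderline responders will be decided by the cut-off instead of by discretion.

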**= pt. will have flexibility to allow scheduling period**

*****

**A**

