**Statistical models.** Separate analyses will be conducted for each negative affect measure. Statistical models will assume that a) data are a mixture of a non-zero continuous component and zeros, and b) the continuous component will follow a beta distribution (i.e., scores will be scaled to be between 0 and 1). Models will include 1) a participant-varying lag-1 autocorrelation term (to handle repeated measures) and 2) a participant-varying probability term governing the occurrence of zeros (to allow for individual differences). Additional covariates will include weekday (categorical, Monday-Sunday), time of day (categorical, 6:00-11:00, 11:00-16:00, 16:00-21:00), age (continuous), and gender (categorical). To test specific hypotheses, additional predictors will be included as needed for a) the beta regression, b) the residual variance term of the beta regression, and c) the probability term governing zeros.

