**Data analysis.**

**Aim 1: To test if negative mood and SI are temporarily relieved and stabilized through acute cannabis use (i.e., negative reinforcement cycle).** We will only use phase 1 data, the 2-week baseline period in which all participants may use cannabis. *Hypothesis 1.1:* We hypothesize that negative affect measures for a) the current random prompt, and b) the prior random prompt (a lag-1 term) will predict 1) greater cannabis use independent of motivating reason (i.e., lower probability for the zero component of the model), and 2) higher scores for motivated cannabis use to improve negative mood. Negative affect measures will therefore be converted to z-scores for this analysis and included as predictors for both the zero and non-zero components of the model. *Hypothesis 1.2:* We hypothesize that the binary indicator for cannabis use in the last hour will predict lower, less variable scores for the negative affect measures. Therefore, the binary use indicator will be included as a predictor for the beta regression residual variance term as well. *Hypothesis 1.3 (exploratory):* There will be within-subject correlates (e.g., concurrent other substance use, social context of use) and between-subject factors (e.g., cannabis use and depression severity, history of suicidal behavior) that moderate relationships between acute cannabis use and negative affect.

**Aim 2: To test if negative mood and SI initially increase with the start of abstinence and then decrease in both mean levels and variability after cannabis wash-out.** We will use phase 1 – 3 data, including predictors for a) group differences (CB-Abst vs. CB-Mon), b) differences by phase (phase 3 vs. phase 1 and phase 2 vs. phase 1), and c) terms for the group by phase interactions. All terms will be included as predictors for the beta regression residual variance term as well. We will only include data for the CB-Abst group with confirmed abstinence for phases 2 – 3. *Hypothesis 2.1:* We hypothesize that CB-Abst will show higher mean negative affect scores and greater variability during phase 2 compared to phase 1, while CB-Mon will show no differences between phases. *Hypothesis 2.2:* We hypothesize that CB-Abst will show lower mean negative affect scores and less variability during phase 3 compared to phase 1, while CB-Mon will show no differences between phases.

**Exploratory analyses:** To further assess heterogeneity in suicidal ideation, we will conduct a set of

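### Only the baseline EMA phase is scheduled around exam weeks and family vacations, so the within-arm phase contrasts of Aim 2 can pick up the school calendar as well as abstinence

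*Protocol*

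**What the plan says.** Protocol, Study Procedures, Baseline Visit (V1), on the two-week phase 1: "We will ensure that this 2-week baseline phase does not coincide with when there are anticipated major deviations from typical patterns of cannabis use". The examples are "e.g., family vacation, exam week".

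The later phases are placed by counting from randomization. Assessment Techniques says: "Two 1-week EMA phases will occur during the randomized period (weeks 1 and 8 post randomization; Figure 1". The schedule table puts V2 at day 14, V5 at day 21, V11 at day 63 and V12 at day 70. No avoidance rule is stated for either week. The Figure 1 key adds that the "pt. will have flexibility to allow scheduling period", but the visit this marks cannot be read from the text at hand.

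Allocation follows phase 1, "using a 1:1 ratio in blocks of 6", and both arms then have the same EMA schedule.

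Under Statistical Analysis, the Aim 2 model contains group, "differences by phase (phase 3 vs. phase 1 and phase 2 vs. phase 1"), and the group-by-phase interactions. Hypotheses 2.1 and 2.2 are expressed as a rise (phase 2) and a fall (phase 3) from phase 1 in the mean and variability of negative affect within CB-Abst, with CB-Mon expected to be unchanged. On covariates: "Additional covariates will include weekday (categorical, Monday-Sunday), time of day", followed by age and gender. None describes exams, vacations or school days.

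**The concern.** Phase 1 is the reference period for both Aim 2 phase contrasts. It is selected for typical weeks, and the periods compared with it are not. The participants are school-based adolescents aged 12-18, so exam and vacation weeks in phases 2 and 3 are foreseeable. The protocol itself treats such weeks as unsuitable for the reference period.

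Two readings are exposed. A change from phase 1 in CB-Abst could be credited to withdrawal or sustained abstinence when part of it comes from the calendar. And the predicted stability of CB-Mon could fail, or appear to hold because influences offset, for reasons unrelated to cannabis. The protocol includes the interaction terms but does not say that the two hypotheses are decided on them.

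**Working it through.** The plan states no figure for this point, so there is nothing to reproduce. The check asks which Aim 2 contrasts a calendar shift can reach.

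**Inputs from the protocol.** Table 1, realistic scenario: 154 participants, taken as 77 per arm; 85 entries in phase 1; 170 entries in all, so (170 - 85)/2 = 42.5, taken as 43, in each later phase. Intra-class correlation 0.09. Power was set for d = 0.2.

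**Assumptions, not in the documents.** A share q of participants has an affected week in the later phase and none in phase 1. That week moves mood by s SD throughout. True change varies between participants with SD 0.2. There is no abstinence effect. Tests are two-sided at 0.05.

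**Expected shift.**
- Within either arm: q × s.
- Group-by-phase interaction: q × s - q × s = 0, because q and s are the same in both randomized arms.

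With q from 5% to 30% and |s| from 0.25 to 0.5, the within-arm shift runs from 0.05 × 0.25 = 0.0125 SD to 0.30 × 0.5 = 0.15 SD, in either direction.

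**Simulated rejection rates with no abstinence effect (4,000 runs).**

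| q | s | Within-arm shift (SD) | CB-Abst | CB-Mon | Interaction |
|---|---|---|---|---|---|
| 0 | 0 | 0 | 4.8% | 5.1% | 5.3% |
| 10% | +0.5 | +0.05 | 29% | 28% | 5.4% |
| 20% | +0.5 | +0.10 | 75% | 74% | 4.2% |
| 20% | -0.5 | -0.10 | 74% | 75% | 5.5% |

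The within-arm tests are misled in whichever direction s points. The interaction test keeps its nominal level.

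**Noise left in the interaction.** The variance of one participant's change without calendar effects is 0.2² + 0.91 × (1/85 + 1/43) = 0.040 + 0.032 = 0.072. Affected weeks add q(1 - q)s²:
- q = 10%, s = 0.5: 0.09 × 0.25 = 0.0225, total 0.094. The standard error rises by √(0.094/0.072) - 1, about 15%.
- q = 20%, s = 0.5: 0.16 × 0.25 = 0.040, total 0.112. The standard error rises by about 25%.

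**Limit of the cancellation.** It requires the arms to be compared as randomized. Data analysis, Aim 2, keeps CB-Abst data in phases 2 and 3 only where abstinence is confirmed, and Protocol non-adherence speaks of abstinence validated over two months. Risks and Discomforts says adolescent users often pause use for sports or family vacations. If confirmed abstinence is related to such weeks, q may differ between the retained CB-Abst participants and CB-Mon, and the interaction then shifts by s times the difference in q. The documents do not allow that difference to be estimated.

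**The case against.** The strongest answer is that the design already contains the safeguard: a concurrent randomized arm on the same schedule, with group-by-phase terms in the model. Specific Aims also words hypothesis 2.1 as holding in CB-Abst but not CB-Mon, which points to a between-arm comparison. This stands for a shift common to both arms. It does not protect the within-arm statements in which the hypotheses are worded, and restricting CB-Abst to abstainers weakens it.

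A reader might infer that phase 1 is a calm period, that the contrasts therefore shift by construction, and that this favours hypothesis 2.1 and works against 2.2. The documents do not support this. The rule is about typical cannabis use, not stress or mood. Exam weeks and family vacations may move mean mood in opposite directions and offset. A shift also requires such weeks to fall in phase 2 or 3.

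A reader might also express the bias as a fraction of the powered effect. Assuming 10-25% of days affected and a shift of 0.3-0.5 SD gives 0.03 to 0.125 SD, or 15% to 63% of 0.2. Those inputs are assumed and all carry one sign, so the range is not an estimate.

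Further points have some force:
- The rule serves Aim 1, which needs use as usual, and cannot carry over unchanged to an arm asked to abstain.
- Specific Aims also compares phase 3 with phase 2, and the asymmetry does not touch that comparison.
- The Figure 1 key mentions scheduling flexibility, and EMA surveys ask about social settings and activities, so some context is collected.
- A covariate or sensitivity analysis could be left to the analysis plan. Even so, that plan cannot reliably rebuild an exam or vacation week that was never recorded, so the data field belongs in the protocol.

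Offsetting effects on the mean need not offset for variability, since shifts of either sign can add spread. But an affected week may cover all or none of a one-week phase, which mainly creates differences between participants, so no size is claimed for variability.

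**Conclusion.** The point holds in limited form. The protocol screens the reference phase for atypical weeks, does not screen the phases compared with it, and plans no calendar term. The within-arm contrasts of phases 2 and 3 with phase 1, including the expected absence of change in CB-Mon, can therefore reflect the calendar. Direction and size are unknown. The 0.05 to 0.10 SD shifts, the rejection rates and the 15-25% loss of precision illustrate assumed inputs and do not forecast this trial.

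No bias is expected in the group-by-phase interaction from a shift common to both arms as randomized. That assurance is weaker once CB-Abst is limited to confirmed abstainers. Aim 1 uses phase 1 only and is not affected by this contrast. The change is a cheap improvement; the documents do not show that Aim 2 is invalid.

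**What to change.** 1. Record each EMA day in all three phases as ordinary school, exam, or vacation/no school. Take this from the school or family calendar rather than from attendance or the participant's judgement, so that it cannot depend on arm.
2. Include that factor, alongside weekday, in the mean, dispersion and zero parts of the Aim 2 model, and repeat Aim 2 on ordinary days only. Phase 1 should contain few exam or vacation days, so the adjustment will rest largely on phases 2 and 3. The ordinary-days analysis does not depend on that adjustment.
3. State that hypotheses 2.1 and 2.2 are judged on the group-by-phase interaction, for both mean and variability, with the within-arm changes as supporting description.
4. Where feasible when setting the V1 date, check that the projected phase 2 (days 14-21) and phase 3 (days 63-70) weeks also avoid known exam and vacation weeks.

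Cost: one data field, one covariate, one sensitivity analysis and a clarifying sentence. Item 4 will delay some start dates and could narrow the choice considerably if both later weeks had to be clear, so it should not be a strict requirement. Items 1 to 3 do not depend on it.
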